#### Paternal outcome measures

Paternal outcomes will be collected to assess potential covariates of a treatment response. Demographic characteristics will be collected and the following measures will be administered to consenting fathers at baseline, 12 weeks RCT, 1 month and 6 months postpartum: EPDS, DASS-21, SF-12 and SLEQ (Fig. 2).

**Fig. 2 Fig2:**
[figure not shown]
Participant flow throughout the trial

### Sample size

This study aims to recruit 120 participants. In 2014, Christchurch New Zealand had 6575 live births [136]. Assuming at least 12% of pregnant women meet criteria for depression / anxiety and accounting for 1 in every 100 pregnancies being twin births, approximately 781 women per year would be eligible for the proposed study in Christchurch alone. A placebo-controlled RCT providing multinutrient supplementation to adults with ADHD [73] showed a between groups effect size of 0.64 on a measure of depression. Other RCTs found a between groups effect size of 0.39 on the EPDS when comparing a multinutrient supplement with a placebo in healthy postnatal women [137] and an effect size of 0.88 on depression outcomes from use of a B vitamin complex compared with placebo for participants with major depressive disorder [138]. Based on these findings, to detect a medium to large effect (0.6) using a two-tailed significance level of 0.05 and a power of 0.8, 45 participants per group would be needed. Assuming an attrition rate of 30% based on the mean dropout rate from the pregnant and postnatal population, 60 participants per group would provide optimal power.

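### Sixty per group does not allow for the assumed 30% attrition: 42 per group remain, not the 45 the plan requires, and power is about 78%

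*Protocol article*

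**What the plan says.** The calculation is in the Sample size section under Methods/design. After citing effect sizes of 0.64, 0.39 and 0.88 from three other trials, the plan takes 0.6 in standardised units as the effect to detect and states its requirement: "using a two-tailed significance level of 0.05 and a power of 0.8, 45 participants per group would be needed". The next step makes an allowance for dropout, and its conclusion is that this number is optimal for power: "Assuming an attrition rate of 30% based on the mean dropout rate from the pregnant and postnatal population, 60 participants per group". The section opens with a target of 120 participants in total, and the Allocation section sets a 1:1 ratio. The section gives no other dropout rate or inflation rule.

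Two statements under Data analysis bear on the point. The EPDS model uses the baseline score as a covariate, and all data are to be analysed by intention to treat with the last observation carried forward.

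**The concern.** The section gives every figure needed to get from the number required to the number recruited, so the step can be checked from the text alone. A reader will take 60 as the number that still leaves 45 evaluable women per group after 30% are lost. It does not. The only power target in the section, 0.8, is tied to 45 per group. If 60 falls short of that after the assumed loss, the design does not have the stated power on its own assumptions. Sample size statements are normally carried over into the results paper, where an unsupported power figure affects how a null result is read.

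**Working it through.** **Inputs, all from the Sample size section:** standardised difference d = 0.6 (SD = 1), two-sided alpha 0.05, power 0.80, 45 evaluable per group, attrition 30%, 60 recruited per group.

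**Step 1: the 45 per group.**
- Normal approximation: n = 2(1.960 + 0.842)²/0.6² = 43.6, so 44.
- Two-sample t-test (noncentral t): n = 44.59, so 45.

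The plan's 45 reproduces by the t-test, so the t-test is used below.

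**Step 2: the attrition allowance.** The number to recruit is n/(1 − attrition).
- From 45: 45/0.70 = 64.3, so 65 per group, 130 in all.
- From 44 (normal approximation): 44/0.70 = 62.9, so 63 per group.

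Neither gives 60. Two other calculations come closer:
- 45/0.75 = 60.0, the figure for 25% attrition.
- 45 × 1.30 = 58.5, so 59, the common slip of adding 30% instead of dividing by 0.70.

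The document does not show which, if either, produced the 60.

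**Step 3: what 60 per group leaves.** 60 × (1 − 0.30) = 42 per group. That is 45 − 42 = 3 evaluable women short per group, or 65 − 60 = 5 randomised women short per group.

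**Step 4: power at d = 0.6, two-sided 0.05.**

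| Evaluable per group | t-test | Normal approximation |
|---|---|---|
| 45 | 80.4% | 81.2% |
| 42 | 77.6% | 78.5% |

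With 42 per group, the effect detectable with 80% power by the t-test is d = 0.619.

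**Step 5: what baseline adjustment would need to recover.** Adjusting for a baseline score that has correlation r with the outcome raises the effective standardised difference to d/√(1 − r²). Setting 0.6/√(1 − r²) = 0.619 gives r = 0.24. The document states no correlation, so any value is an assumption. With 42 per group, r = 0.25 gives 80.1% power, r = 0.4 gives 84% and r = 0.5 gives 88%.

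**Step 6: what carrying observations forward would do.** If all 60 per group are analysed, power depends on how far the dropouts' carried-forward values dilute the effect. The following are assumptions, with the SD unchanged:
- No dilution, d = 0.6: power 90.3%.
- The 30% who drop out carry no effect, so d = 0.70 × 0.6 = 0.42: power 63%.
- 80% power needs an average d of at least 0.516, that is, dilution of no more than 1 − 0.516/0.6 = 14%.

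**The case against.** The strongest objection is that 42 completers per group are not the primary analysis set. Data analysis keeps every participant by carrying the last observation forward, so up to 60 per group are analysed. With no dilution, power would be about 90%. The planned model also uses repeated EPDS measures and adjusts for baseline, and a correlation as low as 0.24 would restore 80% even with 42 per group. The shortfall is also small: a move in detectable effect from 0.60 to 0.62 is slight beside cited effects that run from 0.39 to 0.88. Finally, the text attaches 0.8 to the 45 per group and says only that 60 is optimal.

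Part of this stands. The loss is modest, the unadjusted completers' t-test is not the planned primary analysis, and 80% power after attrition is an inference from the text, though the natural one. But none of it makes the stated derivation correct. The Sample size section treats attrition as a loss to be made up by recruiting more. It does not argue that dropouts still contribute, and it names no correlation. The carried-forward argument can also go the other way: under the assumptions shown, power ranges from 63% to 90%. And the per-protocol analysis of both primary outcomes, also under Data analysis, excludes dropouts. There, 42 per group is the most that 30% attrition leaves, and fewer remain once non-adherent women are excluded too.

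**Conclusion.** The point holds. The 45 per group is right, but 60 per group does not follow from it at 30% attrition. On the plan's own inputs, 42 evaluable women per group remain and power for d = 0.6 is 77.6% by the t-test (78.5% by normal approximation), against a target of 80%. Sixty per group meets the target only if attrition is 25% or less.

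These power figures assume an unadjusted two-group comparison in which dropouts contribute nothing, the only setting in which the section's own calculation makes sense. The loss is two to three percentage points and does not threaten the trial. It needs correcting because the stated sample size and power disagree with the stated assumptions. The power of the analysis actually planned may be higher or lower, and the document does not give the figures to say which.

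**What to change.** Keep 120 women and restate the sentence. Suggested wording: *Sixty participants per group, with 30% attrition, leave 42 evaluable per group, which gives 78% power to detect an effect of 0.6 (80% power for 0.62); 80% power for 0.6 is retained if attrition does not exceed 25%.*

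An alternative is to restate power for the baseline-adjusted model that will be run and to give the assumed baseline to week-12 correlation of the EPDS, with a reason for it. A value of about 0.25 or more brings 42 per group back to 80%. Recruiting 65 per group would also settle it, at the price of ten more women.

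Either restatement costs one sentence and changes nothing in recruitment, conduct or analysis. With the first, the stated power becomes slightly less favourable.

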### Recruitment

Participants will be recruited via social media such as Facebook; posters placed in various community settings such as midwifery, radiology and general practices, and via other media opportunities including local magazines, online news articles and the radio. Midwives and obstetricians will also be contacted and offered brochures to hand out to any potentially interested participants. Advertisements will direct prospective participants to register their interest for the study via an online screening questionnaire (http://www.bit.ly/nutrimum).

### Allocation

#### Sequence generation

A research assistant who is not involved in any other aspect of the study will generate the random allocation sequence using the following website: http://www.randomization.com. Allocation will be arranged in a 1:1 sequence using blocks of four.

#### Allocation concealment

The research assistant will seal the allocation sequence in an opaque envelope and give it to an independent pharmacist who will pre-pack the study intervention and active control accordingly. The pharmacist will seal treatment allocation cards (active or control) in the numbered opaque envelopes in accordance with the allocation sequence. The envelopes will be returned to the study site and stored in a locked drawer. This process ensures that the blind remains for all participants should the blind need to be broken for an individual participant during the course of the trial.

#### Blinding

Both participants and researchers including the data analyst will be blinded to the group assignment of each individual. Following analysis of the primary and secondary outcomes, the blind will be broken and participants will be informed of their treatment allocation. Breaking of the blind will be assessed on a case-by-case basis and will first be discussed with the trial physician.

### Procedure

#### Screening assessment

The online screening questionnaire will assess the eligibility of women who register their interest to participate in the study. Women who do not meet the eligibility criteria for the study will be sent an email encouraging them to speak with their lead maternity carer and consult with listed support services if needed. Women who are eligible from the screening will be contacted and asked further questions before inviting them to visit the research site to provide informed consent. Should a participant not enrol in the trial for more than 2 weeks after the initial screening or register their interest to participate in the study before 12 weeks gestation, they are required to complete a second screening to ensure they are eligible to participate in the study.

#### Baseline assessment

Following informed consent, a baseline appointment will be arranged during which participants will be asked to complete a series of online questionnaires and have their weight and blood pressure assessed. The appointment also involves an assessment of current and past mood and anxiety disorders using the Structured Clinical Interview for DSM-5, Research Version (SCID-5RV) [139]. The Dutch Measure for Quantification of Treatment Resistance in Depression (DMQTR) [117] will be utilized to predict treatment resistance. The DMQTR will be scored based on outcomes from the SCID-5RV, Global Assessment of Functioning from Axis V of the Diagnostic and Statistical Manual of Mental Disorders, Fourth Edition Text Revision [99], Standardised Assessment of Personality – Abbreviated Scale [119] and questions regarding treatment and therapy.

Participants’ partners who agree to participate in the study will provide consent separately. Participants will be given their first bottle of capsules and a capsule organizer containing vanilla sachets in each compartment in order to improve adherence and ensure consistency across treatment arms in smell. They will also be given veral and written instructions on how to take the capsules and titrate the dose over the first week. A blood form and instructions for fasting will also be given to participants who consent to provide blood samples. Participants who provide blood samples will be advised to start taking the capsules the day following blood withdrawal.

#### Trial phase and follow up

Once enrolled in the trial, participants will be required to visit the research site every 4 weeks throughout both the RCT and open label phase until their infant is born. At these visits, participants will complete assessments, collect a new bottle of capsules and return any unused capsules. The next appointment will be scheduled in order to promote participant retention. Two weeks after each visit, participants will be required to complete an online questionnaire at home that assesses mood, side effects and any adverse events. Participants will meet with the researchers for follow up assessments either at the university, at the participant’s home or if possible, over the phone (some participants may find it difficult to travel independently following a caesarean section). Assessments will occur at 1, 6 and 12 months postpartum for all participants including those who discontinue in the trial or deviate from the intervention protocol.

For each visit to the research site, participants will be given a NZD$10 petrol voucher to reimburse travel expenses. A hamper package consisting of products both bought and independently donated will also be provided to participants who complete the RCT phase of the trial in order to congratulate them on the birth of their infant and thank them for their participation. The companies who donate products are not in any other way affiliated with this research.

At the end of the open label phase, participants will decide whether or not they wish to continue taking the treatment and will accordingly be supplied with information on how to obtain the multinutrients.

### Data analysis

Demographic characteristics will be compared across the treatment groups using independent samples *t*-tests in order to test for potential failures of randomization.

For the primary outcomes (EPDS and CGI-I scores), the repeated measures of the outcome variables will be modelled using generalized linear mixed effects regression models using Stata 15 [140]. These models will permit the testing of differences between the multinutrient group and the active control group over the course of the trial. In the case of the EPDS, baseline scores will be used as a covariate factor. For secondary outcomes (e.g. MADRS, DASS), linear mixed effects models will also be used.

The pooled mean scores (and standard deviations) over the course of the trial on each of the primary outcomes will be used to compute estimates of effect size (Cohen’s *d*). Clinical significance between groups will be identified by a minimum of a three point difference in EPDS scores. Clinical significance within groups will be identified by a four point change on the EPDS as described by Matthey [141]. A clinical significant change will be categorised as the following: ‘Recovered’: participants who move from a score of 13 or more at baseline to 11 or less following treatment and whose score has reduced by four points; ‘Improved’: participants whose baseline score reduces by four points post treatment but is still above 13 or more; ‘Deteriorated’: participants whose baseline score increases by four points post treatment; ‘No change’: participants whose pre-post score is less than a four point change.

All data will be analysed on an intention-to-treat basis using the last observation carried forward method and as such will include all participants’ data regardless of treatment compliance. Treatment adherence will be measured by the total number of capsules consumed throughout the trial phases. Only participants who consume 70% or more of the total number of capsules will be considered adherent to the treatment. A per-protocol analysis, which excludes participants with protocol violations (e.g. drop out, non-adherence to treatment consumption) will be performed on the primary outcomes (EPDS and CGI-I) in order to compare differences in treatments responses between participants who were adherent with the treatment and those who discontinued participation or were non-adherent. Outcomes from the open label phase will be compared to the group outcomes from the week 12 observation of the RCT phase using generalised linear mixed effects regression models taking into account participants self-reported use of micronutrients.

To assess the effect of the multinutrient intervention has on infant development, we will compare those infants exposed to the multinutrients versus those infants not exposed to the multinutrients on emotional, cognitive and physical development. Length of exposure to the multinutrients (due to the RCT phase and varying starting points during gestation) and score on the EPDS will also be considered as continuous variables in considering infant outcomes. Hierarchical regression analysis will be run using Stata 15 in order to identify if perinatal/postpartum depression and multinutrient exposure are predictors of improved self-regulation of the infant across the various time points. Descriptive statistics for each participant will be used to compare demographic characteristics between the treatment groups to allow any differences to be controlled.

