### Outcomes

Figure 1 displays the outcome measures of the study and the time points at which each measure will be administered. Demographic characteristics including age, ethnicity, education, occupation, household income, number in household, children and marital status will be collected in a screening assessment. All self-report measures will be independently completed by participants via the web-based data collection system, Qualtrics.

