#### Maternal primary outcome measures

The *Edinburgh Postnatal Depression Scale (EPDS)* [74] is a 10 item self-report questionnaire designed to assess the cognitive and affective symptoms of depression and anxiety over the previous 7 days. The EPDS is the most widely used screening questionnaire for postpartum depression [75] in both research and clinical practice and has also been validated as a screening measure for probable depression during pregnancy [76–78]. Each item on the EPDS is rated on a four-point scale, with a total score ranging from 0 to 30, with higher scores indicating greater levels of distress. A cut off score of 13 has been found to have the optimum specificity and sensitivity in detecting an incidence of major depression in the postnatal period [74]; however, cut off scores during the antenatal period are controversial and culturally dependent; ranging from 4.5 to 13.5 [79]. Despite disagreements in the cut off score for the incidence of major depression during the antenatal period, a cut off score of ≥13 will be used in this study to identify the incidence of perinatal depression. A cut-off score of ≥13 has been used in prevalence studies in New Zealand [5, 6] and has been shown to not miss any women in need of help for their mood in Australian clinical practice [80]. A cut off score of 10 has been shown to be optimal to identify the presence of minor depression in postnatal populations [74]. For this purpose and given the variability of cut-off scores to identify antenatal depression in particular, the present study will use a score of 10–12 to identify minor depression and anxiety and ≤ 9 to identify the absence of perinatal depression and anxiety.

The *Clinical Global Impressions – Improvement Scale (CGI-I)* [81] is a clinician-rated assessment of the change in participant’s symptoms from baseline ranging from 1 (very much improved) to 7 (very much worse). The CGI-I will be administered by graduate students under the supervision of a clinical psychologist and will assess mood, anxiety and global improvements. Participants enrolled in the clinical trial will be asked to rate their own improvement in mood, anxiety and globally at the end of the 12-week RCT phase and again every 4 weeks during the OL phase. The CGI-I has demonstrated high external validity (r = 0.74) [82] and is widely used in clinical trials.

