#### Maternal secondary outcome measures

The *Clinical Global Impressions – Severity Scale (CGI-S)* [81] is a clinician-rated evaluation of symptom severity ranging from 1 (normal, not ill) to 7 (very severely ill). The CGI-S is commonly used in clinical trials and in a routine clinical setting, has shown to be sensitive to clinical change in diagnostically diverse populations including those diagnosed with depression and anxiety [83]. The CGI-S will be administered by graduate students under the supervision of a clinical psychologist and will assess the severity of mood, anxiety and global functioning.

*The Montgomery and Asberg Depression Rating Scale (MADRS)* [84] is a 10 item clinician-rated scale that assesses the frequency, severity and duration of depressive symptoms over the previous week. Each item is rated on a 7-point scale ranging from 0 to 5, with a maximum score of 60. A greater score indicates more severe symptoms. The MADRS demonstrates excellent reliability and good validity [84].The MADRS will be administered by psychology graduate students using the Structured Interview Guide for the Montgomery-Asberg Depression Rating Scale (SIGMA) [85] under the supervision of a clinical psychologist. The SIGMA has demonstrated good to excellent interrater reliability and intraclass correlation (r = 0.93) [85].

*Depression Anxiety Stress Scale 21 (DASS21)* [86] is a 21 item self-report questionnaire with three, seven item subscales measuring the severity of depression, anxiety and stress, each summing to a maximum score of 21 with elevated scores indicating more severe symptoms. Each item on the DASS-21 is rated on a four point scale ranging from 0 (did not apply to me at all) to 3 (applied to me very much, or most of the time). The DASS-21 provides clinical cut-off scores for each subscale ranging from normal to extremely severe. The DASS-21 has been widely used in both clinical and non-clinical populations and has demonstrated strong validity and internal consistency (α = 0.95 depression, 0.90 anxiety, 0.93 stress, 0.97 total score) [87].

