	Inclusion criteria: women aged 16 years and over; 12–24 weeks gestation; low risk singleton pregnancy; free from psychiatric medication for four weeks; score of 13 or more on the Edinburgh Postnatal Depression Scale (EPDS); deemed reliable and compliant with the protocol
	Exclusion criteria: regular vomiting; high risk pregnancy; significant pregnancy complications; known foetal abnormalities; serious current or historical medical condition; known allergy to the ingredients of the intervention; known metabolic condition such as Wilson’s disease, hemochromatosis.; untreated or unstable thyroid disease; known neurological disorder; desire to continue taking prenatal supplements that either exceed the upper limit or are not required for medical purposes (decisions discussed and made on a case-by-case basis)
Study type	Interventional
	Allocation: randomised, parallel assignment; Masking: blinding of people taking and administering the treatment, assessing the outcomes and analysing the results / data
	Primary purpose: treatment
Date of first enrolment	12 April 2017
Target sample size	120
Recruitment status	Recruiting
Primary outcome(s)	Depression and anxiety; Edinburgh Postnatal Depression Scale (time points: screening, baseline, every two weeks until birth and at 1 month and 6 months postpartum)
	Symptom improvement; Clinical Global Impressions Scale – Improvement (time points: baseline, every four weeks until birth and at 1 month and 6 months postpartum)
Key secondary outcomes	Depression; The Montgomery and Asberg Depression Rating Scale (time points: baseline, every four weeks until birth and at 1 month and 6 months postpartum)
	Anxiety; Generalized Anxiety Disorder – 7 (time points: baseline, every two weeks until birth and at 1 month and 6 months postpartum)
	Depression, Anxiety, Stress; Depression, Anxiety, Stress Scale – 21 (time points: baseline, every two weeks until birth and at 1 month and 6 months postpartum)
	Sleep quality; The Pittsburgh Sleep Quality Index (time points: baseline, every four weeks until birth and at 1 month and 6 months postpartum)
	Quality of life; Short Form Health Survey – 12 (time points: baseline, every four weeks until birth and at 1 month and 6 months postpartum)
	Emotion dysregulation; Difficulties in Emotion Regulation Scale - Short Form (time points: baseline, every four weeks until birth and at 1 month and 6 months postpartum)

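### A baseline covariate is stated for the EPDS only, and t-tests for failed randomisation are applied to demographics that include nominal variables

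*Protocol article*

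**What the plan says.** The Data analysis section of the protocol article puts both primary outcomes, EPDS and CGI-I, into generalised linear mixed models and then adds: "In the case of the EPDS, baseline scores will be used as a covariate factor". No covariate is named for CGI-I. The next sentence reads: "For secondary outcomes (e.g. MADRS, DASS), linear mixed effects models will also be used". Nothing is said there about baseline.

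Under Maternal primary outcome measures, CGI-I is defined as a "clinician-rated assessment of the change in participant’s symptoms from baseline". Table 2 (Study integrity) shows which secondary scales have a baseline value. The MADRS entry reads "The Montgomery and Asberg Depression Rating Scale (time points: baseline, every four weeks until birth and at 1 month and 6 months postpartum", and DASS-21, GAD-7, PSQI, SF-12 and DERS-SF also list baseline.

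On comparability of the arms, the Data analysis section compares demographics with independent samples t-tests "in order to test for potential failures of randomization". The variables are listed under Outcomes: "Demographic characteristics including age, ethnicity, education, occupation, household income, number in household, children and marital status will be collected". The paragraph on infant development ends by saying that descriptive statistics "will be used to compare demographic characteristics between the treatment groups to allow any differences to be controlled".

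**The concern.** Two stated choices look poor.

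First, the covariate sentence comes directly after both primary outcomes are named and is worded for one of them. Read plainly, CGI-I is modelled with no measure of baseline severity, and the secondary scales are modelled without their own baselines. In a randomised comparison that does not bias the treatment estimate. It can widen the confidence interval when the data that would narrow it are already in hand.

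Second, the t-test is the only test named for a list that includes ethnicity, occupation and marital status. These have no mean to compare. The stated purpose is also out of reach. The Allocation section describes a computer-generated sequence in blocks of four, prepared by someone otherwise uninvolved and concealed in opaque envelopes. If that process was followed, the null hypothesis of each baseline test is true by design, and a small p-value is chance. If it was not followed, the p-value cannot show that. The risk is that a chance imbalance is reported as a failure of randomisation.

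**Working it through.** **1. The plan's own figure.** Inputs from Sample size: standardised effect 0.6, two-sided alpha 0.05, power 0.80. By the normal approximation, n = 2(1.960 + 0.842)² / 0.6² = 43.6, so 44 per arm. The two-sample t-test gives 44.6, so 45, which is the stated number. The calculation takes no credit for baseline adjustment. With 60 randomised per arm and 30% attrition, 60 × 0.7 = 42 complete. Power at 42 per arm is then 0.785 (normal) or 0.776 (t).

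**2. Own-baseline adjustment on a secondary scale.** The article gives no baseline/follow-up correlation r, so a range is assumed. For one follow-up time, adjustment multiplies the residual variance by 1 − r². Holding the effect at 0.6 unadjusted SDs, power = Φ(0.6·√(n/2)/√(1 − r²) − 1.96):

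| Assumed r | Variance factor | Variance cut | n per arm for 80% power | Power, 42 per arm | Power, 60 per arm |
|---|---|---|---|---|---|
| 0 (unadjusted) | 1.00 | – | 44 | 0.785 | 0.908 |
| 0.3 | 0.91 | 9% | 40 | 0.822 | 0.931 |
| 0.5 | 0.75 | 25% | 33 | 0.888 | 0.967 |
| 0.7 | 0.51 | 49% | 23 | 0.971 | 0.996 |

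The column for 60 per arm is included because the plan analyses all participants with the last observation carried forward. The proportional variance cut is the same in both columns.

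**3. Does the single-follow-up formula overstate the gain?** The models are for repeated measures. For the mean of three four-weekly visits under one common correlation r, the unadjusted variance is (1 + 2r)/3 and the adjusted variance is that minus r². For r = 0.3 this is 0.533 against 0.443 (ratio 0.831). For r = 0.5 it is 0.667 against 0.417 (0.625). For r = 0.7 it is 0.800 against 0.310 (0.388). On that simple structure the single-follow-up figures are not too generous. A correlation that fades with time would change them.

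**4. CGI-I.** A rating of change has no baseline value of its own, so step 2 does not apply. Any gain depends on the correlation between CGI-I and a separate baseline severity measure. The article gives none, so no figure is put on it.

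**5. Baseline tests.** Eight demographics are listed. If each had a valid test at 0.05 and the tests were independent, the chance of at least one significant result under sound randomisation would be 1 − 0.95⁸ = 0.337. This is an illustration only: some of the eight cannot be t-tested at all, and education, occupation and income are plausibly related. With complete dependence the figure would be 0.05.

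**The case against.** The strongest reply is that a journal article condenses the plan, and that silence on secondary outcomes is not exclusion. This largely stands. A mixed model may already carry baseline as one of the repeated responses, and then most of the gain in step 2 is captured. A reader might infer that every secondary outcome loses precision. The article does not support that, and TSQM-11, which rates satisfaction with the treatment, has no evident pre-treatment value.

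The reply on CGI-I is also partly right. Because it is a change rating, the absence of an own-baseline covariate is not an error and probably explains why the sentence is confined to the EPDS. What remains is that a related baseline severity measure is available and not used. Entry at EPDS 13 or more narrows the range of baseline EPDS, which would tend to weaken its correlation with CGI-I.

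A reader might join the t-tests to the remark about controlling differences and conclude that the maternal models take covariates selected by significance test. The text does not say so. The t-tests are given one purpose, a check on randomisation, with no modelling consequence. The remark closes the infant paragraph and refers to descriptive statistics. Infant exposure is also partly non-randomised, since all women may take the multinutrients after week 12, so controlling for confounders there is legitimate. Only choosing them from the differences observed is open to criticism.

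A reader might also want gestational age at entry in every model. That would be a preference; no error in the article calls for it.

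**Conclusion.** The point holds in a limited form. As stated, the EPDS is the only outcome with a baseline covariate, CGI-I has none, and the secondary scales are described without one although at least six have baseline data. The t-test is the wrong tool for the nominal demographics, and significance testing cannot serve its stated purpose under concealed, computer-generated allocation.

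The possible loss is precision, not validity. For secondary scales it is a variance reduction of 9% to 49% forgone, assuming a correlation of 0.3 to 0.7, a single follow-up and a model that makes no other use of baseline. If baseline is already a response in the model, little is lost. At r = 0.5 the gain would equal having 42/0.75 = 56 instead of 42 completers per arm, but that is conditional on the same assumptions and is not shown for CGI-I. The baseline t-tests have no stated effect on the primary analysis; the harm is a possible misreading of chance imbalance.

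**What to change.** - In the CGI-I model, add baseline EPDS as a continuous covariate, or baseline CGI-S if the schedule in Figure 1 has it rated then. Also clear up the baseline time point that Table 2 lists for CGI-I, which does not fit a rating of change.
- For each secondary scale with a baseline value, state that this value is a covariate, unless baseline is already modelled as a response; in that case say so. Leave out TSQM-11.
- Replace the t-tests with a descriptive table of baseline characteristics by arm, and drop the stated aim of testing for failed randomisation. Evidence on that comes from the allocation records.
- In the infant analysis, name the covariates in advance on subject-matter grounds instead of choosing them from observed differences.

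The cost is wording. The EPDS and secondary-scale baselines are already scheduled, and each continuous covariate uses one degree of freedom. The changes should be fixed before the blind is broken.
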